### 5.3. Moderators and descriptive variables

*Sex.* The children's sex (male, female) will be self-reported by students and additionally reported by teachers.

*Disability status of children.* Children formally diagnosed as having a physical or mental disability (e.g., intellectual deficiency) or having adaptation disorders (e.g., conduct disorders) or learning disorders (e.g., language deficits) will be identified by teachers.

*Greenness of neighbourhoods.* The Normalized Difference Vegetation Index (NDVI) will be used to quantify the density of green vegetation associated with the school's zip code. The widely used NDVI is based on the land surface reflectance of colors which is drawn from satellite images of the earth's surface. The index varies between +1 and -1 with higher values indicating higher green vegetation density. We will use 2019 satellite images which are available via the Canadian Urban Environmental Health Research Consortium (CANUE).

*Deprivation indicator of the school.* School's level of deprivation will be quantified using a ranking provided by the Ministry of Education and Higher Education. The ranking is based on a composite score incorporating the proportion of students within each school whose mother completed high-school and whose both parents are employed full time. Schools are classified on a scale ranging from 1 (lowest deprivation) to 10 (highest deprivation).

*Experience with outdoor teaching of teachers.* Teachers' experience with outdoor teaching over the last 3 years (e.g., context, duration) (e.g., did you practice outdoor education in autumn 2022?) and outdoor activities practiced in their leisure time will be assessed with a 6 questions that were successfully used in a previous study on school based outdoor education.

### 5.4. Exploratory variables (measured only at one time point and/or not used as indicators of the effectiveness of the intervention)

*Self-harm.* Self-harm will be self-reported by the child at T2 using the Non-Suicidal Self-Injury (NSSI) subscale of the Self-Harm Inventory. Students will be asked if they ever intentionally engaged in five self-harm behaviors (cutting, burning, hitting, head banging, scratching) (1=yes, 0=no). If a participant answers yes, they will be prompted to report how many times they have engaged in the behavior. The instrument yields two scores: engagement in any self-harm behavior (1=yes, 0=no) and the number of self-harm behaviors reported (continuous).

*Screen time.* Screen time will be self-reported by the child at T3 using 6 items drawn from the Québec Health Survey of High School Students (QHSHSS). The QHSHSS has been successfully used in previous surveys for same aged children from the Direction régionale de santé publique. Students will be asked to report how often they engage in passive screen use (e.g. watching series or movies) and active screen use (e.g. video games, chatting, surfing internet) on weekends and on weekdays on a response scale ranging from 0=never to 7=more than 4 hours per day. The instrument yields two scores: engagement in more than the recommended two hours of screen use on weekdays and on the weekend (1=yes, 0=no).

*Eco-anxiety.* Additionally children will be asked about their eco-anxiety in the context of climate change using 4 self-report questions, adapted from a previous study and refined by experts. Children will self-report at all time points the extent to which they are worried about climate change (1=not at all worried; 4=extremely worried), that these worries motivate them to engage in pro-environmental behaviors or activism (1=not at all; 4=a lot) and that they feel capable of making behavioral changes to help the environment (1=strongly disagree; 4=strongly agree).

## 6. Description of the intervention

### 6.1. Eligibility criteria

Participating schools will be recruited from a list of 280 French language elementary schools in the Canadian province of Quebec, enrolled in a larger study conducted by the Observatoire pour

l'Éducation et la Santé des Enfants (OPES), which aims to document the consequences of the COVID-19 pandemic on 4th grade children's academic achievement ([www.observatoireenfants.ca/en](http://www.observatoireenfants.ca/en)). Additional inclusion criteria for schools are: (a) approval by their school board, (b) access to a greenspace / natural environment (e.g., park, wooded area) on school grounds or within 1 kilometer of the school and (c) having 5-6th grade teachers provide informed and written consent to participate in this study. Inclusion criteria for children to participate in assessments are (a) enrollment in 5-6th grade, (b) providing their assent and (c) having their parents or legal guardians provide informed written consent. As indicated on the information and consent form, participants can withdraw from the study at any time.

## 6.2. Intervention group

The intervention aims to provide approximately 2 hours of exposure to nature per week, in addition to allowing teachers to access a toolkit of pedagogical and mental health activities grounded in positive psychology. The rationale for *Open Sky School* was informed by the growing literature on the benefits of spending time in nature (greenspace) for mental health. For our intervention, exposure to nature consists of teachers bringing their students to the highest quality greenspace within 1 kilometer of their classroom, which could be located on or off campus. For instance, the location could be a forest on campus or a park nearby. Classes will spend a total of 2 hours (i.e. 2 one hour visits or one 2 hour visits) per week for 12 weeks (transportation time included). The exposure time was chosen in line with recent guidelines recommending a minimum of 2 hours per week in nature.

The main component of the *Open Sky School* consists of exposing children to nature. The nature exposure embeds various activities (academic and mental health components), while providing teacher training and support. To this end, we designed an online toolkit of pedagogical and mental health activities that can be conducted outdoors. The mental health activities are rooted in positive psychology (mindfulness, philosophy for children and art therapy) and are designed to improve children's mental health. The pedagogical activities (French language, mathematics and sciences) are aligned on the core academic competencies required by the Ministry of Education of Québec. Teachers will also be allowed to use their own pedagogical activities (if they do, they will be asked to describe their activities), but are encouraged to use those provided in the toolkit, because they were professionally designed and positively appraised in the quality assessment phase. Nevertheless, as our trial primarily aims to reduce mental health problems among children, teachers will be asked to carry out at least 10 mental health activities provided in the toolkit. The toolkit also includes brief video-based modules on best practices and tips for implementing mental health activities outdoors (i.e., how to deal with negative emotions; how children can remain mindful in a noisy environment). Our experts and graduate students in education and clinical psychology will provide teachers with up to 1 hour per week of virtual optional consultation during the intervention to discuss any arising issues related to the intervention and its implementation. Licensed psychologists from the research team will offer psychological support to any participant who reports high levels of psychological distress and reorientate them to appropriate services if needed.

## 6.3. Control group

Six months after the start of the trial, elementary school students (and their teachers) in the control group will receive an unguided version of the intervention, supplemented by an online peer support group. As a significant amount of children in the control group will be in secondary school with different teachers by then (i.e., those who were in 6th grade), we will provide these students with a toolkit of 10 mental health activities, adapted from the activities provided to teachers, that they can practice alone, in addition to support via video-conference, phone or email if they require help from a member of the research team while practicing the activities. As in the intervention group, we will

provide support by licensed psychologists at the request of any child, if for example a child reports high levels of psychological distress, and orient children to appropriate services if needed.

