## 3. Study objectives

*The primary objective* is to test the benefits of time spent in nature on the mental health of 5th and 6th grade elementary students. To be eligible, students must be aged 10-12 years and attend a school with access to a natural space (i.e., park) within a 1 kilometer radius. We hypothesize that students exposed to our 12-week intervention in the 2022-2023 school year will have fewer internalizing (e.g., depression, anxiety) and externalizing (e.g., opposition, inattention/hyperactivity/impulsivity) symptoms and social problems (e.g., bullying/victimization) compared to children in the waitlist control group, who will follow teaching practices as usual. The *secondary objectives* are to study the intervention's effectiveness on children's nature connectedness and other indicators of students' and teachers' wellbeing. Finally, the exploratory objectives of the project are to assess if the effects of the intervention are maintained in the medium-term (i.e., 3 months later) and to examine potential moderating effects, according to various characteristics of (a) the child, i.e., sex, the presence or absence of a diagnosed mental health disorder in the student's file; and (b) the school, e.g., the geographical area, and the vegetation index of greenness surrounding the school.

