## 4. Methods

### 4.1. Design

We will implement a clustered randomized controlled trial with a parallel repeated-measures design. In the trial, 80 to 100 schools with 5th and 6th grade classes will be recruited across Quebec and be randomly assigned to one of the following conditions: 1) *Open Sky School* intervention (intervention group) and 2) teaching as usual (waitlist control group, who will receive the intervention the following school year if it is effective). We will randomize at the school level rather than at the class level to allow for more than one class within the same school to take part in the project while avoiding possible contamination effects. In the context of our project we define our nature intervention by exposing children to natural environments during school hours and including any activity that promotes learning or mental health. The available natural space must be located near the school, within a 1 kilometer radius, and can be, for instance, an urban park, wooded area or waterfront. In other words, we are interested in engaging children in nature (in urban or rural areas) and providing access to academic or mental health activities in order to promote their wellbeing.

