### 4.4. Recruitment strategy and timeline

Participating schools will be recruited from a list of 280 French language elementary schools in the Canadian province of Quebec, enrolled in a larger study conducted by the Observatory for Children's Education and Health, which aims to document the consequences of the COVID-19 pandemic on 4th grade children's academic achievement ([www.observatoireenfants.ca/en](http://www.observatoireenfants.ca/en)). Eligible schools will receive an initial invitation letter by email (December 2022), containing a 90 second informative video, which they will be asked to distribute to their 5-6th grade teachers. In the invitation letter, 5-6th grade teachers will be invited to attend an online information session describing their involvement in the *Open Sky School* project. All interested teachers will be sent an information and consent form. Once teachers consent to take part in the study, they will distribute information and consent forms to students and students' parents. To maximize recruitment potential, we will also post a recruitment flyer via social networks inviting interested participants to contact us via email to receive the aforementioned information describing their involvement in the project.

Baseline assessment will take place from March 6 to 10, 2023 and post-test assessments will be conducted from June 5 to 12, 2023. The weekly 2-hour nature visits will take place from March 13, 2023 to June 2, 2023. The follow-up assessments will be administered from September 18 to 23, 2023. To encourage participation throughout the study, teachers will be compensated \$100 CAD for evaluating their students' mental health symptoms before and after the intervention (up to \$200 CAD total). Children can choose to participate in a draw to win gift cards to a local bookstore. More specifically, we will draw two \$50 CAD gift cards per class for children who complete questionnaires at baseline and immediate follow up, and ten \$100 CAD gift cards for children who complete the follow-up assessment. Figure 1 shows a flow chart of the inclusion of participants.

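### Control-arm access is not tied to the T3 assessment: on the stated timing it opens about 5 to 17 days before T3, so the exploratory maintenance contrast is not cleanly against usual teaching

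*Protocol*

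**What the plan says.** All references are to the protocol.

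**When and whether controls get access**
- Section 6.3, on the program: "Six months after the start of the trial, elementary school students (and their teachers) in the control group will receive an unguided version". For control children who have moved to secondary school, "we will provide these students with a toolkit of 10 mental health activities"; no separate date is given for them.
- Section 4.1: the control group are those "who will receive the intervention the following school year if it is effective".
- Section 1: access comes in the fall of 2023, without a condition. Usual teaching is described only for March to June 2023.
- Section 9.3: control teachers who choose to take part in the 12-week program are surveyed in winter 2024.

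**The calendar (Section 4.4)**
- On T1: "Baseline assessment will take place from March 6 to 10, 2023".
- On the intervention period: "The weekly 2-hour nature visits will take place from March 13, 2023 to June 2, 2023".
- On T3, the last measurement: "The follow-up assessments will be administered from September 18 to 23, 2023".

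**What T3 is for**
- Section 3 lists, among the exploratory objectives, to "assess if the effects of the intervention are maintained in the medium-term (i.e., 3 months later".

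**The concern.** T3 is the only time point that can answer whether the effect lasts. That question needs a control arm that has not yet had the program. If controls are given the activities shortly before T3, a small T3 difference has two explanations: the effect has faded in the intervention arm, or the control arm has begun to benefit. No section provides for recording when each control school or child gains access, or what they use before T3, so the two could not be separated afterwards.

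The access statements also disagree on a second matter. Section 4.1 makes access depend on the program being effective, while Sections 1 and 6.3 promise it outright. This concerns what controls are promised. It does not add to the T3 bias, but it has to be settled in the same edit.

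**Working it through.** **Check of the calendar.** From 13 March to 2 June 2023 is 12 school weeks. 12 weeks × 2 h = 24 h, which agrees with the full dose in Section 7. The visit dates are therefore consistent with the stated program.

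**Control access under Section 6.3.** The start of the trial is not defined, so each March reading is taken in turn.

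| Start of trial | Plus 6 months | Days to T3 (18 to 23 Sept) |
|---|---|---|
| 6 March (baseline opens) | 6 Sept | 12 to 17 |
| 10 March (baseline closes) | 10 Sept | 8 to 13 |
| 13 March (first visits) | 13 Sept | 5 to 10 |

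The overall range is 5 to 17 days before T3. Counting from the December 2022 invitations would put access in June 2023, which is also before T3. That reading does not fit Section 6.3, which expects the former 6th graders to be in secondary school by the time of access, so it is set aside.

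**Largest control exposure by T3.** This assumes immediate uptake at the program's own pace of 2 h per week.
- Shortest gap: 5/7 × 2 = 1.4 h; 1.4/24 = 6% of the dose.
- Longest gap: 17/7 × 2 = 4.9 h; 4.9/24 = 20% of the dose.

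**Share of each recall window that follows access**
- Social Behaviour Questionnaire, two months (Section 5.1), taken as 61 days: 5/61 = 8% to 17/61 = 28%.
- Depression and affect scales, two weeks (Section 5.2): 5/14 = 36% to 14/14 = 100%.

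These shares measure overlap in the calendar. They are not estimates of bias.

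**Sensitivity to rounding.** Section 4.3 calls T3 three months after the intervention ends. From 2 June to 18 to 23 September is 108 to 113 days, and at 30.44 days per month this is 3.5 to 3.7 months. The protocol therefore rounds by half a month or more. Half a month is about 15 days. Added to 6 to 13 September it gives 21 to 28 September, which is during or after T3. The ordering holds on a literal count but does not survive loose rounding.

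**The other access statements.** The fall of 2023 (Section 1) and the following school year (Section 4.1) allow access before or after T3. A survey in winter 2024 (Section 9.3) fits a 12-week program begun in September or somewhat later. None of them requires access to wait for T3.

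**The case against.** The strongest reply is that the protocol prints no access date in September. The dates are derived from an undefined start, the margin is only 5 to 17 days, and the protocol rounds months elsewhere. Sections 1 and 4.1 leave room for access after T3. That the secondary-school children receive their activities at the same moment is also inferred. All of this stands, and it means that access before T3 is not established as fact. It does not remove the point: Section 6.3 is the only statement that counts access from the start of the trial, both March anchors place it before T3, and nothing protects T3.

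A second reply is that access is not exposure. The control version is unguided, Section 9.3 speaks of control teachers who choose to take part, and the secondary-school children would practise alone. This also stands. It limits the likely effect to partial dilution.

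Two stronger readings are tempting. A reader might infer that the T3 contrast is lost altogether. The figures do not support this, since controls could have had at most about 5 of 24 hours, without guidance. A reader might also infer that the main result is compromised. It is not: T2 is in June 2023, before access opens on either March count, and Section 3 places maintenance among the exploratory objectives. Section 8 names all three times under one longitudinal model, so this reassurance applies to the contrast from T1 to T2 itself.

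**Conclusion.** The point holds in a limited form. The access statements are inconsistent and are not tied to T3. If Section 6.3 is followed literally from a March 2023 start, access opens about 5 to 17 days before T3, and the T3 comparison is immediate access against delayed access that has just begun.

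If the program works, the likely direction is a T3 difference pulled toward zero. The size cannot be computed because uptake is not given; the upper bound on exposure is 4.9 of 24 hours, or 20% of the dose, assuming full-pace uptake from the first day. For the primary questionnaire, 8% to 28% of the recall window would follow access.

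Severity is moderate, because only an exploratory objective is affected and the comparison from T1 to T2 is untouched. Confidence is high that the passages need reconciling, and lower that access actually came before T3.

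**What to change.** 1. Reconcile Sections 1, 4.1, 6.3 and 9.3 on whether and when the control arm gets access, including whether access depends on effectiveness. Define the start of the trial. Which arrangement is right is for the sponsor to settle.
2. State access relative to T3. T3 keeps an unexposed comparator only if T3 is complete before access opens, and the text should say whether this is so.
3. Where access did or will precede T3, define and report T3 as immediate versus delayed access. Keep all randomised children in the analysis, in line with the intention-to-treat approach in Section 8. Report control access dates and uptake before T3 where recorded, and do not read a null T3 difference as loss of effect.
4. Do not restrict T3 to control questionnaires completed before access. If access opens on 6 to 13 September, no control questionnaire from 18 to 23 September would remain. If access dates vary, the restriction selects one arm on an event after randomisation.

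The cost is wording plus, where it can still be collected, one access date and a short note of use per control school or child. The reference list carries an access date in September 2024, so the T3 dates have probably passed. In that case the work is to document what happened, using dates recorded at the time, and to word the T3 claim to match.

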## **7. Implementation of the intervention (fidelity)**

The teachers will fill out an online logbook in which they will indicate information about each nature visit. They will provide information on the activities they chose to carry out (from our toolkit or others of their choice), the duration of these activities, where the activity was carried out and the total time spent outdoors. They will record if they watched our training videos, if they encountered any problems and the amount of time they spent with our supervisors. This information will be used to evaluate the adequacy of the implementation of our intervention. To fully comply with implementation, there must be of a total of 24 h of intervention (2 h per week for 12 weeks) and a minimum of 10 mental health activities from the toolkit must be carried out. Classes that do not achieve a minimum of 80% completion and comply with content 90% of the time will be excluded from sensitivity analyses. Information contained in the logbooks will be evaluated independently by two researchers and we will analyze inter-rater agreement to ensure the consistency of the codification of the information provided.

## **8. Statistical analyses and power**

All analyses will be conducted at the cluster level, i.e., at the school level. Dependent variables will be measured on a continuous scale. Child mental health will be assessed at T1, T2, T3. A longitudinal ANCOVA, as described in Liu et al (2009), will be used to estimate the main and moderating effects described above. The characteristics of the intervention group and the control group will be compared at the class level, where means (e.g., socioeconomic deprivation) could be added to the model as covariates, in the unlikely event that randomization would not have balanced the two groups. A total of 80 to 100 schools (with a minimum of 40 classes if only one class per school participates) will detect small effects (power >90%). An intention-to-treat analysis approach will be used to increase the internal and external validity of the project. The analyses will include any child for whom at least one questionnaire has been completed at least one measurement time and the multiple imputations will be used in case of significant loss to follow-up.

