### 4.2. Randomization

Randomization will occur after baseline assessments. Once randomization has occurred, it will not be possible to blind researchers and participants within our design. A simple computer algorithm will be used to randomly allocate schools to two parallel and balanced conditions (intervention or control; 1:1 while considering class sizes) by an independent researcher not involved in the study. This will ensure that all schools have an equal opportunity to be allocated into one of the two groups. In the event that multiple teachers from the same school consent to participate, they will be allocated to the same experimental condition to avoid contamination effects.

**Figure 1.** Flow chart of inclusion of participants.

[figure not shown]

Note. a 280 schools in 29 school boards were initially eligible. 4 school boards encompassing 32 schools did not agree to participate and were therefore removed from the recruitment process. b If more than 100 teachers consent to participate, we will randomly select 100 teachers to participate in the trial. c Parents and students must provide informed consent for students to participate in the assessments. Students who do not participate in assessments will still participate in the Open Sky School program. d In the event that multiple teachers from the same school consent to participate, they will be allocated to the same experimental condition to avoid contamination effects. If recruitment targets at the pre-selected school are not met, we will advertise online.

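### Grade determines who changes school before T3 but is not a prespecified covariate, which can cost avoidable precision on the exploratory T3 contrast

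*Protocol*

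**What the plan says.** - **School move.** Protocol section 6.3 acknowledges the split when it describes what controls receive in the autumn: "As a significant amount of children in the control group will be in secondary school with different teachers by then", meaning those who were in 6th grade. Section 4.4 dates T3 to 18–23 September 2023, in the next school year.
- **Allocation.** Section 4.2: "A simple computer algorithm will be used to randomly allocate schools to two parallel and balanced conditions", "1:1 while considering class sizes". Class size is the only factor named.
- **Model.** Section 8: "All analyses will be conducted at the cluster level, i.e., at the school level". A longitudinal ANCOVA "will be used to estimate the main and moderating effects described above". Class-level means may be added as covariates if randomisation fails to balance the arms; deprivation is the one example.
- **Moderators.** Section 3 limits the child-level list to sex and diagnosed disorder. For the school it gives examples: "the geographical area, and the vegetation index of greenness surrounding the school". The section 5 table and section 5.3 add teacher experience, disability status and school deprivation. Grade appears in none of these.
- **Status of T3.** Section 3 makes maintenance at three months an exploratory objective.

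**The concern.** Grade is an eligibility criterion (section 6.1), so it is on file for every class before allocation. It fixes which children go through a change of school between T2 and T3. Adjustment for T1 scores cannot absorb an event that comes after T1. If the move affects symptoms, 5th-grade and 6th-grade schools will differ at T3 for a reason unrelated to the intervention. In a school-level analysis with few classes per school, that difference goes into the between-school residual.

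The covariate rule in section 8 does not deal with this reliably. It is discretionary and it is triggered by observed imbalance. When the arms happen to be balanced on grade, the rule leaves grade out, yet the grade variance still sits in the residual and still widens the interval. At stake is the precision of the trial's only assessment of whether effects last.

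**Working it through.** **Plan's own figure.** Section 8 claims power above 90% for small effects with 80 to 100 schools. It states no alpha, numerical effect, ICC, class size or T1 correlation, so the figure cannot be reproduced. Assume two-sided 0.05, d = 0.2, m = 20 children per school and 40 schools per arm. Power is then 81.7% at ICC 0.05 with no T1 correlation, and 91.1% at ICC 0.05 with r = 0.5. The second setting is the reference below.

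**Inputs from the protocol.** 80 to 100 schools at 1:1 gives k = 40 to 50 per arm. The lay abstract speaks of 80 to 100 classes and the Figure 1 note caps teachers at 100, so there are about 1.0 to 1.25 (100/80) classes per school.

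**Assumptions.** One single-grade class per school, half of the schools in each grade. Let g be the T3 gap between grades, in SD, that T1 does not explain. The protocol gives no value; the range shown is 0.1 to 0.5.

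**Step 1: chance imbalance in 6th-grade share.** SD = √(2 × 0.25 / k).
- k = 40: √0.0125 = 0.112, a 95% range of ±22 percentage points.
- k = 50: √0.0100 = 0.100, a 95% range of about ±20 points.

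**Step 2: variance of the T3 contrast with grade in the model.** V₀ = 2 × [1 + (m − 1) × ICC] × (1 − r²) / (k × m) = 2 × 1.95 × 0.75 / 800 = 0.003656, so SE = 0.0605.

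**Step 3: variance with grade left out.** V₁ = V₀ + g² × 0.0125.

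| g (SD) | SE without grade | SE ratio | Power at d = 0.2 without grade (with grade: 91.1%) |
|---|---|---|---|
| 0.1 | 0.0615 | 1.02 | 90.2% |
| 0.2 | 0.0645 | 1.07 | 87.3% |
| 0.3 | 0.0691 | 1.14 | 82.4% |
| 0.5 | 0.0823 | 1.36 | 68.0% |

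Both terms of V₁ scale with 1/k, so the SE ratios are the same at k = 50.

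**Step 4: cross-check.** At g = 0.3 the variance ratio is (0.0605/0.0691)² = 0.77. A separate simulation of class means on the same assumptions also gives 0.77.

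**Step 5: sensitivity to ICC at g = 0.3.** At ICC 0.10, V₀ = 2 × 2.9 × 0.75 / 800 = 0.00544 and the SE ratio is √(0.00656/0.00544) = 1.10. At ICC 0.20, V₀ = 2 × 4.8 × 0.75 / 800 = 0.00900 and the ratio is √(0.01013/0.00900) = 1.06.

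**Step 6: mixed schools.** If every school contributed the two grades in equal parts, the 6th-grade share would not vary between schools and the added term would vanish. Real schools fall between the two extremes.

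**The case against.** The strongest reply is that this is an omission rather than an error. The covariate list for an exploratory time point is commonly left to the SAP, which was not available for this review and may name grade. The section 8 list is open-ended, and so is the school-level moderator list, so grade is unnamed rather than excluded. A reader might infer that a balance check could never bring grade in. That is not so: the check looks at class characteristics, and the share of 6th graders is one. What remains is that the protocol itself fixes a discretionary, imbalance-triggered rule, and that rule recovers no precision when the arms are balanced.

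A reader might also infer that the T3 contrast is biased. The documents do not support that. Schools are randomised, 6th graders move in both arms, and omitting grade leaves the estimator unbiased. In a given allocation a 20-point imbalance with a 0.3 SD gap would shift the estimate by 0.20 × 0.3 = 0.06 SD, but that is chance imbalance, which a valid cluster-level standard error already covers.

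Two further objections stand in full. The size depends on a grade gap, grade mix, ICC and class size that the protocol does not give, and at 0.1 SD the gain is close to nil. And T3 is exploratory, while the T2 comparison precedes the school move and is not affected by it.

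**Conclusion.** The point holds as one about precision and prespecification. Grade determines the school move, the protocol recognises this in section 6.3, and the analysis section does not take it up. On the stated assumptions the T3 standard error is inflated by about 2% (gap 0.1 SD), 14% (0.3 SD) or 36% (0.5 SD). The inflation is smaller with a higher ICC or with schools that contribute both grades. The loss is material only if the unexplained grade gap is about 0.3 SD or more. It is no threat to the validity of the T3 contrast.

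**What to change.** In section 8, prespecify grade as a fixed covariate with a grade-by-time term, regardless of observed balance: child grade, or the share of 6th graders where the unit is the school. The time interaction matters because the move can act only at T3. Report the T3 effect by grade as an exploratory moderator analysis, and add grade to the moderators in sections 3 and 5.3.

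Use grade as an allocation factor in section 4.2 only if allocation has not yet taken place. Randomisation was due after the March 2023 baseline and the reference list carries a September 2024 access date, so the analysis change is probably the only part still open.

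The cost is one or two degrees of freedom out of 80 to 100 schools. No new data are needed.
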